#### 4. RESEARCH DESIGN

##### 4.1. JUSTIFICATION OF METHODOLOGICAL CHOICES

##### Choice of the mixed approach

The study aims to understand the patient experience when introducing a new tool in caregiver-patient communication, throughout the care pathway. The introduction of a new mediation tool in patient care can impact patient-professional interactions. It is therefore necessary to understand how this tool, whether personalized or generic, will support the patient throughout their care.

This is why a comprehensive approach to the interactions between patient/professional and patient/entourage, during the informational and educational processes mediated by a personalized or generic tool, is indicated as a study design.

Also, the R3DP-P study is anchored in a comprehensive approach to the interactions between patients and professionals, as developed in health anthropology (16,17):

- Ethnographic approach (i.e. based on observations of information situations, particularly during interactions between professionals/patients, professionals/professionals, patients/patients, etc.) and more generally anthropological (based on individual semi-directive interviews exploring the patients' experience, health education, health literacy) (18).

- Educational Sciences approach (based on the same interviews and observations) to understand the information situations that arise during the patient's journey, describe the knowledge dissemination and knowledge construction circuits of the different actors, to understand the transposition work carried out by professionals during interactions with patients (19).

In addition, a more quantitative approach complements the comprehensive and didactic approach and allows us to question the impact of the integration of the model on the patient's understanding of the pathology and their level of health literacy. This approach will be carried out via the validated HLSEU-Q16 literacy questionnaire, the pathology understanding and satisfaction questionnaire, created internally, and taken up internationally in the Scott study (13) (appendix 1, 2 and 3).

## 4.2. STUDY SCHEME

This is a single-center study, conducted within the Urology, Andrology and Renal Transplantation Department of the Bordeaux University Hospital. It is a mixed study (qualitative and quantitative) based on observations (interaction situations), interviews (professionals and patients) and questionnaires (patients).

### Patients

- Interventional study, prospective randomized, in 2 parallel open arms: one having a preoperative visit with a personalized 3D printed kidney model, the other with a generic 3D printed kidney model,
- Prospective inclusion.

Patients will be randomized with a 1:1 ratio to two groups:

- Group 1: Personalized 3D printed model group,
- Group 2: Generic 3D printed model group.

### Professionals

Non-interventional study of the experience of professionals when caring for patients who have benefited from a preoperative visit using a personalized or generic 3D printed kidney model. Note that a study of the experience of professionals before the implementation of 3D models

was carried out as part of the Rein-3D Print PERSONALIZE– Pro Before– Hors Loi Jardé project (reference number CER-BDX 2023 – 64).

STUDY SCHEME

[figure not shown]

### 4.3. RANDOMISATION METHOD

The randomization list is established by the statistician of the Methodology Center (USMR of the Bordeaux University Hospital) before the start of the research.

The numbers of the 2 strategy groups are balanced with a 1:1 ratio, without stratification factor. A document describing the randomization procedure is kept confidentially within the Methodology and Data Management Center.

## 5. ELIGIBILITY CRITERIA

### 5.1. INCLUSION CRITERIA

#### Patients

- Age  $\geq 18$  years,
- Scheduled surgical management by coelioscopic partial nephrectomy with robotic assistance (first management for a unilateral or bilateral kidney tumor),
- Free, informed and signed consent for the UroCCR database,
- Free, informed and signed consent for the Rein-3D Personalize protocol,
- Person affiliated or beneficiary of a social security scheme.

#### Professionals

- Professional working with patients treated in the Urology, Andrology and Renal Transplantation department of the Bordeaux University Hospital for at least two months before the implementation of the 3D tools,
- Free, informed and signed consent.

### 5.2. EXLUCSION CRITERIA

#### Patients

- Metastatic at the time of inclusion,
- History of kidney cancer,
- Single kidney at the time of inclusion,
- Absence of preoperative CT scan or poor quality CT scan not allowing reliable 3D modeling,
- Person subject to a legal protection measure (judicial safeguard, guardianship or curatorship),
- Difficulty understanding and expressing oneself in French.

## Professionals

- Professional on an internship of less than 6 months,
- Professional without contact with patients.

### 5.3. FEASIBILITY AND RECRUITMENT TERMS

This is a single-center study including patients treated in the Urology, Andrology and Renal Transplantation Department of the Bordeaux University Hospital. The patients are all included in the UroCCR database and, given the prospective inclusions recorded in the database in 2022, the inclusion potential is much higher than the expected 4 patients/month (223 patients operated on for robot-assisted partial nephrectomy in 2022).

## RECRUITMENT METHODS

### Patients

Patient inclusion will be prospective and will take place after the consultation with the urologist.

All adult patients meeting the inclusion criteria and scheduled for a laparoscopic partial nephrectomy with robotic assistance for a kidney tumor will be offered the study.

The principal investigator will provide the participant with an information note on the study and a consent form.

### Professionals

All professionals meeting the inclusion criteria who care for patients monitored in the Urology, Andrology and Renal Transplantation Department of the Bordeaux University Hospital will be included.

The SHS researchers or the principal investigator will present the study to the professionals themselves and give them the information note relating to the study including a consent form.

## 6. RESEARCH STRATEGY(S)/PROCEDURE(S)/PRODUCTS

### 6.1. STRATEGY

#### Patients

Upon inclusion in the study, patients will be randomized into 2 arms, corresponding to the different information media used during the information consultation:

1. Personalized 3D printed model group: discussion time with the physical three-dimensional model printed of the kidney to be operated on as information support
2. Generic 3D printed model group: discussion time with a physical three-dimensional model printed as information support, from a case of eight models, and corresponding as closely as possible to the situation

#### Professional population

No specific intervention

## 6.2. EXPERIMENTAL AND COMPARISON PROCEDURE

### 6.2.1 CUSTOM PRINTED 3D MODEL GROUP

For patients randomized to the “personalized” group, a 3D model of the kidney and tumor will be performed by the surgeon, based on the preoperative scan, using Synapse 3D software (Fujifilm). This model will then be printed using the Stratasys printer acquired in partnership with the IUT of Bordeaux and located on the IUT site (sending of the 3D files (.stl) anonymized by the software to the IUT engineer in charge of printing). The 3D model printing time is approximately 15 days after the scans are performed.

[figure not shown]

3D TUMOR KIDNEY MODELS

For group 1, the 3D printed personalized model is presented to the patient by the surgeon during a dedicated consultation between D-30 and D-7 before the operation, accompanied by anatomical comments and simple surgical strategies. During this visit, the patient will then be able to take charge of and manipulate the personalized model.

### 6.2.2 GENERIC PRINTED 3D MODEL GROUP

For patients randomized to the "generic" group, the surgeon has a case containing 8 3D-printed kidney models (made using the Stratasys printer acquired in partnership with the IUT of Bordeaux and located on the IUT site).

These 8 models cover:

- The different locations: superior, equatorial and inferior; anterior and posterior; external border and internal border,
- Hilar tumors,
- The endophytic or exophytic characteristic,
- The different sizes: cT1a, cT1b and cT2,
- Modal vascularization or the presence of a 2nd artery.

The surgeon will select from the generic models the one that most closely matches the patient's situation based on the size and location of the kidney tumor. The 3D printed generic model will then be presented to the patient by the surgeon during a dedicated consultation between D-30 and D-7 before the operation, accompanied by anatomical comments and simple surgical strategies. The patient will then be able to take charge of and manipulate the generic model.

## 7. RESEARCH PROCESS

### 7.1 RESEARCH CALENDAR

## Patients

- Duration of the inclusion period - 18 months, - Duration of participation - between 3 and 6 months.

## Professional population

Participation throughout the study, as part of the observation of patient pathways. Duration of participation for professionals: 24 months.

Total duration of the research: 38 months (inclusion, monitoring, analysis and valorization).

## 7.2 SUMMARY TABLE OF PARTICIPANT MONITORING

### Patients

|                                                          | STUDY PERIOD               |                    |                 |                                |                      |            |                             |                  |
|----------------------------------------------------------|----------------------------|--------------------|-----------------|--------------------------------|----------------------|------------|-----------------------------|------------------|
|                                                          | Enrolment                  | Allocation         | Post-allocation |                                |                      |            | Close-out                   |                  |
| Timepoint                                                | T0
(First consultation) | T1
(T0 + 1 day) | (T1 + 15 days)  | T2
(30 to 7 days before D0) | T3
(T2 + 15 days) | T4
(D0) | T5
(T4 + 15 to +45 days) | T6
T5+15 days |
| ENROLEMENT                                        |                            |                    |                 |                                |                      |            |                             |                  |
| Eligibility screen                                       | X                          |                    |                 |                                |                      |            |                             |                  |
| Informed consent                                         | X                          |                    |                 |                                |                      |            |                             |                  |
| Allocation                                               |                            | X                  |                 |                                |                      |            |                             |                  |
| INTERVENTION                                      |                            |                    |                 |                                |                      |            |                             |                  |
| Modeling virtual 3D-model (according to randomized arm)  |                            |                    | X               |                                |                      |            |                             |                  |
| Printing 3D-model (according to randomized arm)          |                            |                    | X               |                                |                      |            |                             |                  |
| Preoperative information according to randomized arm     |                            |                    |                 | X                              |                      |            |                             |                  |
| Surgery                                                  |                            |                    |                 |                                |                      | X          |                             |                  |
| ASSESSMENTS                                       |                            |                    |                 |                                |                      |            |                             |                  |
| HLSEU-Q16 questionnaire (health literacy)                |                            | X                  |                 |                                |                      |            | X                           |                  |
| Questionnaire (knowledge of disease and planned surgery) |                            | X                  |                 |                                | X                    |            |                             | X                |
| Questionnaire of satisfaction                            |                            |                    |                 |                                |                      |            |                             | X                |
| Semi-directive interview                                 |                            | X                  |                 |                                | X                    |            |                             | X                |
|                                                          |                            |                    |                 |                                |                      |            |                             |                  |
|                                                          |                            |                    |                 |                                |                      |            |                             |                  |

(R) : recherche  
(S) : soins courants  
\* 15 jours devant être pris en compte pour

l'impression et la transmission du modèle 3D imprimé, l'imagerie doit avoir été réalisée au moins 15 jours avant la consultation d'information.

## □ TEMPORAL SCHEME FOR PATIENT FOLLOW UP

[figure not shown]

## Professionnels

|                                                              | Presentation of the study to the entire team - T0 | Between implementation and 1 year after first inclusion | Interview with professional              |
|--------------------------------------------------------------|---------------------------------------------------|---------------------------------------------------------|------------------------------------------|
|                                                              | When setting up the study                         |                                                         | 1 year after the first patient inclusion |
| Information                                                  | ✓                                                 |                                                         |                                          |
| Collection of consent (R)                                    |                                                   | ✓                                                       |                                          |
| Semi-directed interview conducted by a researcher in SHS (R) |                                                   |                                                         | ✓                                        |

## 7.3 INCLUSION VISIT (T0)

### 7.3.1 COLLECTION OF CONSENT

During the inclusion visit, the investigating physician informs the participant and answers all their questions regarding the objective, the nature of the constraints, the foreseeable risks and the expected benefits of the research. He also specifies the participant's rights in the context of research and checks the eligibility criteria.

A copy of each information note (Rein-3D PERSONALIZE and UroCCR) and the consent form is then given to the participant by the investigating physician. After this information session, the participant

has a period of reflection. If the participant agrees to participate, the latter and the investigator write their first and last names in clear text, date and sign the two consent forms in two original copies (for participation in the Rein-3D PERSONALIZE project and for collecting the data necessary for analysis in the UroCCR database). These must be signed before any clinical or paraclinical examination required by the research is carried out. The different copies of the information note and the consent form are then distributed as follows:

- An original copy of each information note and each signed consent is given to the participant.
- The other original copies are kept by the investigator (even if the participant moves during the research) in a safe place inaccessible to third parties.

### 7.3.2 VISIT DETAIL

#### Patients

The inclusion visit is carried out by the investigator. Before any examination related to the research, the investigator obtains the free and informed consent of the patient (or their legal representative if applicable).

The patients included are received in the urology department, as part of the management of their pathology. The inclusion visit is carried out by the investigator. A member of the SHS research team may participate in the visit as an observer.

#### Professionals

A collective meeting to present the study is held one month before the start of the interviews by the investigator and the SHS research team who present the study during formal or informal times set up in the department with the professionals.

The SHS research team will act under the responsibility of the investigator.

The SHS researchers inform and answer all questions concerning the objective, the nature of the constraints, the foreseeable risks and the expected benefits of the research. They also specify the possibility for the participant to withdraw from the research at any time, and verify the eligibility criteria. A copy of the information note (with the contact details of the SHS research team and the clinical research associate of the Rein 3D Print PERSONALIZE project) and the consent form is then given to the professional by the research team. The research team then collects the consent to participate.

- An original copy of the information note and the signed consent is given to the participant.
- The other original copy will be kept by the investigator (even if the participant moves during the research) in a safe place inaccessible to third parties.

### 7.3.3 VISIT/RANDOMIZATION APPROACH

Patient randomization will be performed immediately after the inclusion consultation. It will be done directly on the UroCCR database web interface.

When an investigator wishes to perform randomization, after prior verification of the participant's eligibility, he will connect with his codes on the website: <http://uroccr.fr>. He will complete the "Research / Kidney-3D PERSONALIZE" tab and confirm all the patient's eligibility criteria. After validation of the content, inclusion and randomization will be performed. The interface will

immediately communicate to the investigator the patient's unique number in the research and the result of the randomization. The result of the randomization will only be communicated to the patient at the Exchange and Information Consultation (T2).

## 7.4 FOLLOW-UP VISITS

### 7.4.1 PREOPERATIVE PERIOD (T1)

Patients are seen, between the inclusion visit and the information consultation, by a member of the SHS research team at the hospital or at home according to their preferences at T0 +15 days at the latest. This exchange time corresponds to a face-to-face interview during which the following will be discussed:

- ☐ Collection of the patient's experience since the first symptoms leading to the visit to the urology department,
- ☐ Collection of socio-demographic data,
- ☐ Collection concerning exchanges with those around them about the disease,
- ☐ HLSEU-Q16 literacy questionnaire collected via a tablet on UroConnect,
- ☐ Questionnaire on understanding renal anatomy and surgical issues via a tablet on UroConnect.

### 7.4.2 EXCHANGE AND INFORMATION CONSULTATION (T2)

Patients are seen between 30 days and 7 days before the operation by a member of the surgical team. The purpose of this discussion time is to allow the patient to express their questions, share their doubts or misunderstandings in relation to their medical situation and the scheduled intervention. It may lead to explanations on anatomy and simple surgical strategies by the member of the surgical team participating in this interview.

The two interventional groups (Personalized 3D Printed Model Group and Generic 3D Printed Model Group) are presented with the model as a discussion support.

The explanations given to patients are not standardized within the framework of the study in order to be closer to usual practice.

The duration of this visit as well as the presence or absence of an accompanying person will be collected.

A member of the SHS research team may participate in the visit as an observer.

### 7.4.3 SECOND PREOPERATIVE PERIOD (T3)

Patients are seen between the information consultation and the operation by a member of the SHS research team at the hospital or at home according to their preferences at the latest at T2 +15 days. This exchange time corresponds to a face-to-face interview during which the following elements will be discussed:

- ☐ Collection of the patient's experience since the last interview,
- ☐ Collection concerning exchanges with those around them about the disease,
- ☐ Questionnaire for understanding renal anatomy and surgical issues with a tablet on UroConnect.

### 7.4.4 SURGERY (T4)

No specificity for the study but, as for any patient included in UroCCR, the characteristics and technical progress of the surgical procedure will be collected. There will be, due to the study, no modification of the surgical technique of robot-assisted partial nephrectomy as envisaged by the surgeon.

#### 7.4.5 POSTOPERATIVE VISIT (T5)

The post-operative assessment will be collected. There will be, due to the study, no modification of the post-operative consultation other than the potential presence of a member of the SHS research team during the consultation.

#### 7.5 END OF RESEARCH VISIT (T6)

##### Patients

The research data collection ends no later than 15 days after the last postoperative consultation.

Patients will be seen by a member of the SHS research team at the hospital or at home, according to their preferences. This exchange time corresponds to a face-to-face interview during which the following elements will be discussed:

- ☐ Collection of the patient's experience since the last interview,
- ☐ Collection concerning exchanges with those around them about the disease,
- ☐ HLSEU-Q16 literacy questionnaire via a tablet on UroConnect,
- ☐ Questionnaire on understanding renal anatomy and surgical issues via a tablet on UroConnect,
- ☐ Satisfaction questionnaire via a tablet on UroConnect.

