3D models will be presented to the patients according to the allocated study group during a preoperative education consultation. All patients will complete questionnaires about their health literacy level, their knowledge of kidney anatomy and tumor and their satisfaction about the using 3D-printed kidney models as educational mediation tools. Semi-structured interviews will be conducted at three different times: between the first consultation with the surgeon and the preoperative education consultation, between this second consultation and the surgery and after the post-operative consultation.

Primary outcome:

To study the effects of using a personalized versus a generic 3D-printed kidney model as a mediation tool on patients' experience and interactions with carers, before and after partial nephrectomy.

This is a mixed-type study designed to combine data from different collection tools (observations, interviews and questionnaires). The criteria studied are:

For the patient:

- Qualitative assessment of the patient experience
- Changes in the average score of the HLSEU-Q16 literacy questionnaire - Level of understanding of renal anatomy and of the surgical issues

For the carers:

- Qualitative assessment of changes in practice following the integration of 3D models into the department

Secondary outcomes:

1. Description of interactions between carers and patients, specifying the situations and the environments, the practice, vocabulary and content of the discourse used during the entire care process.
2. Comparison of the differences in speech and terminology used when using the different tools during interactions between patients, carers and patients' entourage with systematic analysis of interviews.
3. Studying the use of the 3D-printed kidney model introduced during the medical information consultation up to the post-operative visit by describing the life of the model throughout the entire care process (from the inclusion visit to the post-op visit).
4. Comparison of the patient's understanding of anatomy and surgical strategy according to the type of tool (personalized vs generic 3D printed model) before and after the surgery (T1, T3 and T6).
5. Comparison of the level of health literacy between the two groups at different times with changes in the average score on the literacy questionnaire (HLSEU-Q16: European Health Literacy Survey Questionnaire; T1 and T6).

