| 2/ What I know about my disease:                                                                                                                                                                | 2/ Ce que je sais de ma maladie :                                                                                                                                                                                                 | True /
Vrai | False /
Faux | Don't know / je ne sais pas |
| 2.1- My kidney is bearing a tumor                                                                                                                                                               | 2.1- Mon rein est porteur d'une tumeur                                                                                                                                                                                            |                |                 |                             |
| 2.2- The tumor is located in the mid part of my kidney                                                                                                                                          | 2.2- La tumeur est située dans la partie médiane de mon rein                                                                                                                                                                      |                |                 |                             |
| 2.3- The tumor is in close contact with the kidney vessels                                                                                                                                      | 2.3- La tumeur est en contact étroit avec les vaisseaux du rein                                                                                                                                                                   |                |                 |                             |
| 2.4- The tumor is in close contact with the collecting system                                                                                                                                   | 2.4- La tumeur est en contact étroit avec le système collecteur                                                                                                                                                                   |                |                 |                             |

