| 3/ What I understand about my planned surgery                                                                                                                                                   | 3/ Ce que je comprends de l'intervention chirurgicale prévue                                                                                                                                                                      | True /
Vrai | False /
Faux | Don't know / je ne sais pas |
| 3.1- My surgeon will try to remove the tumor only                                                                                                                                               | 3.1- Mon chirurgien essaiera d'enlever uniquement la tumeur                                                                                                                                                                       |                |                 |                             |
| 3.2- My surgeon will remove the entire kidney                                                                                                                                                   | 3.2- Mon chirurgien va enlever tout le rein                                                                                                                                                                                       |                |                 |                             |
| In case of tumor only removal my surgeon will have to cut the kidney itself to separate the tumor from surrounding healthy tissue. This may lead to:
3.3- bleeding with a risk of hemorrhage | Dans le cas d'une ablation de la tumeur uniquement, mon chirurgien devra couper le rein lui-même pour séparer la tumeur des tissus sains qui l'entourent. Cela peut entraîner
3.3- des saignements avec un risque d'hémorragie |                |                 |                             |
| 3.4- opening the collecting system with a risk of urine leakage                                                                                                                                 | 3.4- l'ouverture du système collecteur avec un risque de fuite d'urine                                                                                                                                                            |                |                 |                             |

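### The knowledge questionnaire is worded for a tumour still in place and surgery still to come, yet is re-used unchanged after the operation, so change to T6 on the tumour items cannot be interpreted

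*Protocol*

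**What the plan says.** The knowledge questionnaire is scheduled three times. Section 7.4.1 places it at T1, before the information consultation. Section 7.4.3 places it at T3, between that consultation and surgery, as the "Questionnaire for understanding renal anatomy and surgical issues with a tablet on UroConnect". Section 7.5 places it at T6 as the "Questionnaire on understanding renal anatomy and surgical issues via a tablet on UroConnect". The follow-up table in Section 7.2 has one row for it, "Questionnaire (knowledge of disease and planned surgery", ticked at T1, T3 and T6. T6 follows both the operation (T4) and the post-operative visit (T5).

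Appendix 2 is the only version in the protocol. Its answers are true, false or don't know.
- Part 2 opens with "2.1- My kidney is bearing a tumor" and goes on, also in the present tense, to the tumour's location and contacts.
- Part 3 is headed "3/ What I understand about my planned surgery". Items 3.1 and 3.2 are in the future tense; 3.2 reads "3.2- My surgeon will remove the entire kidney".
- The French column uses the same tenses, so this is not a translation artefact.

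Secondary objective 4 (Section 2.2) compares understanding between arms before and after the operation. The Abstract specifies "before and after the surgery (T1, T3 and T6". Section 9.3.4 studies how understanding evolves, using this questionnaire and the interviews, and compares the groups.

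**The concern.** A repeated knowledge test measures change in knowledge only if the correct answer to each item stays the same or is re-keyed in step with the facts. Here the facts change between T3 and T6 because the tumour has been removed. A patient who knows this and answers item 2.1 literally will say false. A patient with the same knowledge who takes the item to be about the disease as it was will say true. Whichever key is used at T6, one of the two is scored as not knowing.

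The within-patient change to T6 is what is at stake. Part 2 is the most exposed, and it is the part about the patient's own tumour, where a personalised model might be expected to differ most from a generic one (hypothesis 1, Section 1.2). A fall in part 2 scores after surgery could be reported as lost understanding when none was lost.

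**Working it through.** The protocol gives no figure for this questionnaire, so there is nothing to reproduce. The check counts and classifies the items in Appendix 2.

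**Step 1: item count.** Part 1 has 8 items, part 2 has 4 and part 3 has 8: 8 + 4 + 8 = 20.

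**Step 2: does the literal answer change once a single tumour has been removed?**

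| Items | Before surgery | At T6, read literally |
|---|---|---|
| 1.1–1.8 | General kidney facts | No change |
| 2.1 | True | Changes to false |
| 2.2–2.4 | True or false, depending on the patient | Can change only where it was true |
| 3.1 | True (future tense) | Can change, because no operation is still to come |
| 3.2 | False | Still false if the kidney was preserved |
| 3.3–3.8 | Conditional or general statements | Tense out of date, but truth does not clearly reverse |

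**Step 3: range.** Assume one point per item and a patient-specific key for 2.2 to 2.4.

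| Case | Items affected | Share of 20 | Share of part 2 | Share of part 3 |
|---|---|---|---|---|
| 2.1 only | 1 | 1/20 = 5% | 1/4 = 25% | 0/8 = 0% |
| 2.1 and one of 2.2–2.4 | 2 | 2/20 = 10% | 2/4 = 50% | 0/8 = 0% |
| 2.1–2.4, all true before surgery | 4 | 4/20 = 20% | 4/4 = 100% | 0/8 = 0% |
| The same, plus 3.1 read literally | 5 | 5/20 = 25% | 4/4 = 100% | 1/8 = 12.5% |

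**Step 4: effect on change within a patient.** Take a patient who answers every item correctly at T3, understands just as well at T6, reads the items literally, and is scored on the pre-operative key. Part 2 falls from 4 to 4 − 1 = 3 at the least affected end, and to 4 − 4 = 0 at the most affected. A total falls from 20 to between 19 and 15. No understanding was lost. Re-keying 2.1 to false at T6 moves the penalty to the patient who answers in retrospect. It also fails for some patients with bilateral tumours, who are eligible under Section 5.1 and for whom 2.1 may still be true.

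**Step 5: effect on the T6 comparison between arms.** Both arms get the same form. Let *k* be the number of affected items and *p* the share of patients who read them literally. For patients of equal understanding, the expected loss is *p* × *k* points in each arm. Randomisation makes *k* similar in expectation. If *p* is also the same in both arms, the losses cancel in the difference and leave extra variation between patients. A net shift needs *p* to differ by arm, and the protocol gives no basis for any value of *p*.

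**Step 6: what is untouched.** T1 and T3 both precede surgery, so the comparison between them is unaffected. Part 1 and items 3.2 to 3.8 remain usable at T6, with the proviso on 3.2 in the table.

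**The case against.** The best defence is that the protocol states no answer key, total score or scoring rule for this questionnaire. Visit-specific keys are often left to a statistical analysis plan, which is not shown. Section 7.5 sets the T6 questionnaire within a face-to-face interview, where a misreading could be noticed, and Sections 9.3.3 and 9.3.4 interpret questionnaires alongside interview content. The main criterion is qualitative and objective 4 is secondary. Section 3.2 also sets out a comparison around the presentation of the model, which T1 and T3 serve without difficulty.

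Much of this stands. It makes every count of lost points conditional on an assumed key, and it keeps the matter to one time point of one secondary objective.

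It does not remove the problem. A scoring rule written later cannot tell from a true or false response which way the patient read the item; only the wording or an instruction can, and the wording is fixed in the appendix. The interview setting is not matched by any written instruction, and Section 11.3.2 also allows collection on paper or by automatic sending to patients.

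A reader might go further and infer that the fault works against the better-informed arm, producing a false difference between groups. The documents do not support that. It would require one arm to read the items more literally than the other, and nothing in the protocol says or implies this.

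**Conclusion.** The point holds for the change from T1 or T3 to T6 on part 2, on item 3.1, and on any total that includes them. The size is 1 to 5 of 20 items (5% to 25%), and 1 to 4 of the 4 items in part 2. This rests on one point per item, a patient-specific key for 2.2 to 2.4, and a single tumour that was resected with the kidney preserved. The upper end needs 2.2 to 2.4 all to have been true before surgery and 3.1 to be read literally. The T6 contrast between arms becomes noisier, with no bias shown.

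Two broader readings should be set aside. One is that six items are affected because 3.2 is also in the future tense; its answer is false before a partial nephrectomy and stays false after it. The other is that T6 scores as a whole cannot be compared with earlier ones; part 1 and items 3.2 to 3.8 can be.

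**What to change.** Either of two changes is enough.

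1. **Change the T6 form.** Put items 2.1 to 2.4 and 3.1 in the past tense, or place them under an instruction to answer for the time before the operation. Key them to each patient's pre-operative imaging and operative report, which also deals with bilateral tumours and operations that did not go as planned. Leave the T1 and T3 forms alone. The cost is an edit to one electronic form and its paper equivalent, and a slight departure from the published wording at T6.

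2. **Leave the form and change the analysis.** Limit the T1, T3 and T6 trajectory to part 1 and items 3.2 to 3.8, and assess part 2 on T1 to T3 only. Item 3.2 should be checked against the operative report where the kidney was not preserved. This needs only a rule in the analysis plan and also works for data already collected. The cost is that the questionnaire then says nothing about retained knowledge of the patient's own tumour after surgery, which would rest on the interviews.
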